# OUTdoor Swimming as a nature-based Intervention for DEpression (OUTSIDE): study protocol for a feasibility randomised control trial comparing an outdoor swimming intervention to usual care for adults experiencing mild to moderate symptoms of depression

**DOI:** 10.1186/s40814-023-01358-3

**Published:** 2023-07-13

**Keywords:** Open water swimming, Sea, Lake, River swimming, Cold water swimming, Cold water, Wellbeing, Depression, Anxiety, Health-related quality of life, Health and social care resource use, Social prescribing, Nature-based interventions, RCT

## Abstract

**Background:**

Depression is common and the prevalence increasing worldwide; at least 1 in 10 people will experience depression in their lifetime. It is associated with economic costs at the individual, healthcare and societal level. Recommended treatments include medication and psychological therapies. However, given the long waiting times, and sometimes poor concordance and engagement with these treatments, a greater range of approaches are needed. Evidence for the potential of outdoor swimming as an intervention to support recovery from depression is emerging, but randomised controlled trials (RCTs) evaluating clinical and cost-effectiveness are lacking. This study seeks to investigate the feasibility of conducting a definitive superiority RCT, comparing an 8-session outdoor swimming course offered in addition to usual care compared to usual care only, in adults who are experiencing mild to moderate symptoms of depression. Feasibility questions will examine recruitment and retention rates, acceptability of randomisation and measures, and identify the primary outcome measure that will inform the sample size calculation for a definitive full-scale RCT. This study will also explore potential facilitators and barriers of participation through evaluation questionnaires, focus-group discussions and interviews.

**Methods/design:**

To address these aims and objectives, a feasibility superiority RCT with 1:1 allocation will be undertaken. We will recruit 88 participants with mild to moderate symptoms of depression through social prescribing organisations and social media in three sites in England. Participants will be randomised to either (1) intervention (8-session outdoor swimming course) plus usual care or (2) usual care only. Both groups will be followed up for a further 8 weeks.

**Discussion:**

If findings from this feasibility RCT are favourable, a fully powered RCT will be conducted to investigate the clinical- and cost-effectiveness of the intervention. Findings from the definitive trial will provide evidence about outdoor swimming for depression for policymakers and has the potential to lead to greater choice of interventions for adults experiencing symptoms of depression.

**Trial registration:**

Current controlled trial registration number is ISRCTN 90851983 registered on 19 May 2022.

**Supplementary Information:**

The online version contains supplementary material available at 10.1186/s40814-023-01358-3.

## Background

Globally, depression has a lifetime prevalence of 10.8% [1], with the rate significantly increasing during the Covid-19 pandemic [2]. The total annual cost of mental ill health in the UK is at least £117.9 billion [3]. This continues to grow nationally and globally [4].

Treatment guidelines recommend a range of psychological therapies, medication and physical activity as evidence-based interventions for depression [5, 6]. However, outcomes from these interventions are variable and do not appear to be reducing the prevalence [7]. Psychological therapy and medications have modest recovery rates (45–50%) [8] with both low adherence to medication [9] and talking therapy completion rates [10]. Exercise as a treatment for depression is also recommended and appears to be effective for some [11]. However, only 66% of males and 58% of females meet UK government recommended levels of physical activity (150 min of moderate activity or 75 min of vigorous activity per week) [12]. Therefore, a greater range of approaches are required in addition to medication, talking therapies or the more standard forms of exercise.

There is growing evidence that access to the natural environment (green and blue spaces) is linked to improving mental health [13, 14]. Green exercise initiatives show great promise in improving wellbeing. Mind commissioned an evaluation of 25 ecotherapy projects, in which participants were encouraged to be active outdoors and found measurable improvements with 7 out of 10 people experiencing significant increases in wellbeing, social inclusion, healthier lifestyles, greater connection with the natural world and adoption of environmentally informed behaviours [15]. However, not all types of green and blue exercise will equally engage all people, for instance, due to injury or poor motivation to do the activity. Therefore, a range of nature-based activities are required so that people can find and choose a preferred activity with which they can best engage.

There is growing evidence that access to green and blue spaces is linked to improving mental health [13, 14]. Green exercise initiatives have shown promise in improving wellbeing. MIND [15] commissioned an evaluation into over 25 ecotherapy projects, in which participants were encouraged to be active outdoors and found measurable improvements with 7 out of 10 people experiencing significant increases in wellbeing, increased social inclusion, healthier lifestyles, greater connection with the natural world and adoption of environmentally informed behaviours. However, not all exercises will engage all people, for instance, due to injury or poor motivation to do specific activities (reported by members of the patient and public inclusion group for the current study). Therefore, a range of activities are required, including those which are nature based, so that people can find an activity with which they can engage. Qualitative research has also indicated that undertaking nature-based activity within water offers additional benefits that could contribute to improved mental health and wellbeing. These include being “present” [16], a sense of escape from everyday life [17] and developing resilience [18] as a risky activity becomes an enabling one [19]. The experience of activity in water has been described as “transformative, connecting and reorientating” as participants enjoy feeling better after a swim, a sense of connection to nature and others and developing different perspectives about themselves and the world [20]. There are a range of possible physiological mechanisms as a result of activity in water that may contribute to an impact on mental health (e.g. cold water vagus nerve stimulation [21], “post swim” stress hormone responses [22], cross-adaptation and reduced cortisol responses [23, 24] and reductions in inflammatory responses [25]). As outdoor swimming is a nature-based activity that is increasing in popularity [26], and has the potential to affect a range of outcomes including mental health [27–29], it is worthy of further study.

The water around the UK is cold all year, and therefore, open water swimming in the UK is considered cold water swimming. Typically, summer water temperatures are between 15 and 20 °C, and conversely, water temperatures can become very cold in winter between 0 and 7 °C [31]. As such, there is a seasonality to outdoor swimming, particularly for those being introduced to the activity, as it is recommended that they start in the summer months [32] when the water temperatures are at their highest. They can then choose to continue as the water cools. As participation in groups is strongly encouraged, for safety reasons, many groups will modify the activity reducing the time in the water during colder months; wear neoprene gloves, boots and a wetsuit in winter [32], and try different locations where the water temperature may be higher, and some may also decide not to swim but maintain contact with the group during this time. These are all potential mitigations to the seasonal nature of the activity. As the effect on depressive symptoms of such an intervention has not been investigated by a robust RCT, the potential mechanisms of the effect have also not been fully investigated; whilst outdoor swimming may be seasonal in the UK, it does not mean all outdoor swimming activity would stop.

Further trials using robust designs, including RCTs incorporating mixed methods, are required to understand if outdoor swimming has potential as a treatment for depression [33]. As outdoor swimming can also be hazardous [25], well-planned empirical research is needed to determine if it is safe and as helpful as early research suggests, before recommending it as an evidence-based treatment for depression. Likewise, it is essential to determine whether sufficient numbers of people with depression will be interested in participating in the intervention, who it most benefits and if it is less attractive to some members of the population and whether measures can be put in place to address this.

This is a protocol for a feasibility RCT, comparing an 8-session outdoor swimming course offered in addition to usual care, with usual care only, in adults who have mild to moderate symptoms of depression. Our aim is to assess the feasibility of undertaking a definitive superiority RCT, comparing an 8-session outdoor swimming course offered in addition to usual care compared to usual care only, in adults who have mild to moderate depression. Objectives are as follows: (1) to determine recruitment and retention rates, acceptability of randomisation and measures, and identify the primary outcome measure that will inform the sample size calculation for a definitive full-scale RCT and (2) to understand potential facilitators and barriers of participation through evaluation questionnaires, focus-group discussions and interviews.

## Methods/design

### Design and sample size

This is a parallel-group, pragmatic superiority feasibility RCT with 1:1 allocation to an 8-session outdoor swimming course plus usual care or usual care only. Using random permuted blocks, we will randomly allocate 88 people meeting eligibility criteria to receive the eight 1-h sessions of a swim course provided by trained and experienced outdoor swim coaches, on top of usual care or usual care only. Stratification is by location (three sites in England). Participants will complete measures at baseline (T0), post swim course or the equivalent time point for the usual care only group (T1) and again after a further 8 weeks (T2) for follow-up (see Fig. 1).

**Fig. 1 Fig1:**
[figure not shown]
Schedule of enrolment, interventions and assessments

The sample size was based up on Teare et al.’s recommendation for pilot studies [34], where a total of 35 participants would be required per arm. To account for 20% drop-out, a total of 88 participants will be required. This drop-out rate is an estimate based on our previous single-arm study [28].

Evaluation questionnaires, semi-structured focus groups and interviews will be conducted with participants from both arms (at T2) to gain further understanding of barriers and facilitators to recruitment and retention in the study and, for those in the swimming arm, the barriers and facilitators to the swimming courses. Anyone who chooses not to participate will also be invited to complete a questionnaire and, if they had been consented to the study, attend an interview. In addition, social prescribers referring potential participants and the swim coaches providing the courses will be invited to attend focus groups to share their perspectives.

The study design was informed in consultation with a public and patient involvement (PPI) group and supported by the PPI co-applicant (SC). Members of the PPI group had previously participated in introductory swim courses, set up introductory swim courses for people with mental health difficulties or had lived experience of depression. The PPI group were instrumental in guiding the study team to focus on the participants’ journey through the trial, developing the participant information sheets and helping to inform the recruitment strategy.

### Participants

Participants will be recruited through social prescribing teams local to the swim locations and through self-referral to the study following advertising on social media. Social prescribing link workers, usually employed or commissioned through general practice in the National Health Service (NHS) in England, dedicate time to supporting people with their mental health needs and promoting awareness of activities that their patients can participate in to help themselves. NHS England’s mental health long-term plan [35] recommended the introduction of 1000 new social prescribers by the end of 2020/2021 and with more to follow.

Inclusion criteria are that participants will be as follows:Aged 18 years or olderAble to give informed consent to participateHave mild to moderate severity depression, as determined by the 9-question Patient Health Questionnaire ([PHQ-9] scores 5–19 inclusive)Have a self-reported ability to swim a minimum distance in a heated pool. This varies by swim location, which differs between the 3 sites: (1) sea (50 m, 2 length of a normal swimming pool); (2) lake (25 m, 1 length of a normal swimming pool); and (3) no swimming experience is required for outdoor unheated swimming pool (lido).

People will be excluded on the following basis:Risk of suicide or recent suicidal intent or attempts or self-harm requiring medical treatmentOther mental health problems to a severe degreeNot able to speak English to a level that would enable them to understand safety instructionsHistory of cardiac abnormalities (e.g. ischaemic heart disease/angina and congestive heart failure)Immediate (first degree) relative history of cardiac events (GP consultation will be required for inclusion).Respiratory conditions triggered by cold such as poorly controlled exercise-induced asthmaColdwater urticaria (a skin reaction to cold that appears within minutes after cold exposure)Non-freezing cold injuries/Raynaud’s

### Measures

#### Demographics

A questionnaire will be completed by participants to collect key demographics (e.g. age, gender).

#### Primary feasibility measures

Participant recruitment rates (numbers recruited per week)Study retention (percentage of participants with 95% confidence intervals)Intervention retention (percentage of intervention participants attending at least 4 of the 8 swim sessions with 95% confidence intervals)Data completeness (%)

#### Secondary feasibility measures

Experience of participation for participants, link workers and coachesThe number and type of serious adverse reactions

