### Procedure

See Fig. 1 for the SPIRIT [55] schedule of enrolment, interventions and assessments. Participants with mild to moderate symptoms of depression will be sought through social prescribing services and self-referral. The study will be advertised by social prescribers and elsewhere through social media. Informed consent will be obtained from each participant by the recruitment team (HM, AB, RC and AJ). Potential participants will be given a copy of the study participant information sheet and will have the opportunity to discuss the study with the research assistant (RA) by phone or video call before signing the consent form (a copy of which can be obtained from the corresponding author). Written and verbal consent will be received at least 24 h after participants are given the participant information sheet.

To assess the risk at entry to the trial, initial information will be gathered from self-reported online health history questionnaires about the participant’s medical history. The research assistant will also perform the PHQ-9 at the consenting phone call. The health history questionnaire and PHQ-9 will be assessed by the medical team RC and AB (both psychiatrists) who will evaluate the risk. Following this, those deemed at high risk will be contacted by the medical team via a phone call, and those deemed as low risk or where further information is required will be contacted by the research assistant or other members of the research team either by phone or email and answers discussed with the medical team if necessary. During the study, if a concern is raised by the participant, swim coaches or a study team member the medical team will contact those involved and recommend the actions to be taken, if any.

Once the participant has consented to participate in the trial, the participant will complete the full set of baseline measures. Measures will be completed online, on paper or with an RA present by telephone depending on participant preference. Participants who do not meet eligibility criteria at the baseline assessment will be referred to social prescribers to be offered alternative activities.

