#### Course structure

The focus of these courses will be the safe enjoyment of the water rather than becoming an expert swimmer. The swim coach will phone or text participants the night before each session and meet them outside the facilities. They will walk into the facility together and will be shown where to change and what to bring with them to the water’s edge.

All swimmers will be supervised by the course staff (who have basic life support, lifeguard qualifications and have attended courses on mental health first aid and mental health awareness training), and they will only swim if it is safe to do so. It is not possible to offer a completely standardised course as local conditions will dictate what can be achieved in the sessions.

Outdoor swimming courses should be offered when the water temperatures are at their highest. Therefore, the intervention group will start their swimming course no earlier than the beginning of August and courses will finish no later than the middle of November. The sessions will include basic swimming skills (Lido only), safety, hazard awareness and risk assessment and development of competency to deal with moderate challenges when in the water, including floating and in-water-based skills. However, alternative arrangements and session plans will be available for adverse weather conditions that do not allow the swim to take place at the normal time.

Wetsuits will not be provided as the water will be between 15–20 °C), but participants can use their own wetsuit if they wish. It will be made clear to participants that they should leave the water immediately should they feel uncomfortably cold. Although the session is an hour in length, the maximum in-water time will be 30 min. The remaining 30 min will be split between the pre-swim briefing and post-swim rewarming. After exiting the water, participants will return to the changing areas and change into warm dry clothes. Participants will be encouraged to have a hot drink. Risk assessments will be carried out on the day by the swim coach and lifeguard. Participants will consent for the research team to provide the swim coaches with details of medical conditions, swim experience and emergency contact details. At all times, clients will be monitored closely for signs of hypothermia.

During the course, participants will be supported to find existing groups or form their own so that they can continue to swim safely after completion of the course.

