### Serious adverse event monitoring

A protocol for identifying and independently assessing serious adverse events will ensure that such events are addressed in a timely fashion and responded to, including if a serious adverse event is classified as potentially study related. Serious adverse events and their classification will be reported to the Trial Steering Committee (TSC), and action will be taken as deemed necessary. Where deemed in the best interests of participants, the study intervention may be discontinued.

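### The listed safety measure counts serious adverse reactions only, although the trial already collects all serious adverse events; report the events by arm, with the study-related subset shown separately

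*Protocol article*

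**What the plan says.** Under Secondary feasibility measures, the protocol article lists two items: participants', link workers' and coaches' experience, and the "number and type of serious adverse reactions". The second is the only quantitative safety measure listed. Planned data analysis commits to summary statistics for the feasibility measures, so this is the safety figure that the plan undertakes to report.

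Serious adverse event monitoring uses a different term. It provides for "A protocol for identifying and independently assessing serious adverse events will ensure that such events are addressed in a timely fashion", and treats relatedness as a later step, "including if a serious adverse event is classified as potentially study related". It then states: "Serious adverse events and their classification will be reported to the Trial Steering Committee (TSC").

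Three other places bear on the point:

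- The Background says that "well-planned empirical research is needed to determine if it is safe and as helpful as early research suggests".
- Course structure says "At all times, clients will be monitored closely for signs of hypothermia".
- Procedure routes any concern raised by a participant, coach or team member to the medical team.

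None of these three defines a safety outcome.

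**The concern.** In ordinary usage an adverse reaction is an event judged to have been caused by the intervention. The plan thus collects the wider set and names the narrower one as its measure, with two consequences.

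First, the reported figure depends on a judgement of cause, made event by event. In a sample this small, moving one event across the line could change the whole result. Serious deterioration in mood or self-harm, in either arm, would enter the measure only if someone attributed it to the intervention.

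Second, people who receive no swimming course can hardly have a reaction to it. The control arm would show whether serious events are more frequent with swimming than without, whatever anyone thinks of the cause of each. The listed measure does not use it.

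Contact also differs by arm. Swimmers hear from a coach before each of 8 sessions and are seen at those they attend. The article describes no matching contact for usual care between T0 and T1. A count by arm is therefore fair only if both arms are asked the same question at the same times.

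At stake is what the definitive trial inherits: a short list of attributed events, or serious event counts by arm.

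**Working it through.** **1. Sample size, reproduced.** Design and sample size gives 35 per arm, 20% drop-out and 1:1 allocation. 35 / (1 − 0.20) = 43.75, rounded up to 44 per arm; 44 × 2 = 88. This matches the stated 88.

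**2. The two sections side by side.**

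| Event | Identified, classified and sent to the TSC | In the listed measure |
|---|---|---|
| Serious, swim arm, judged related | Yes | Yes |
| Serious, swim arm, judged unrelated | Yes | No |
| Serious, usual-care arm, judged unrelated | Yes | No |
| Serious, usual-care arm, judged related to a study procedure | Yes | Possibly; the term is not defined |
| Non-serious, swim-related | Outside this section | No |

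Rows two and three are the mismatch. The trial holds these events, but the named measure leaves them out. Row four is why the control arm is best described as contributing essentially nothing, and not as zero by definition.

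**3. What a count of serious events can show at this size.** For zero events in n people, the exact upper 95% limit is 1 − 0.025^(1/n) two-sided and 1 − 0.05^(1/n) one-sided.

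- n = 44: 1 − 0.025^(1/44) = 8.0%; 1 − 0.05^(1/44) = 6.6%.
- n = 35 (after the assumed drop-out): 10.0% and 8.2%.

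The article gives no event rates, so the next figures use assumed ones. The chance of at least one event among 44 swimmers is 1 − (1 − p)^44:

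| Assumed rate p | Chance of at least one event |
|---|---|
| 1% | 36% |
| 2% | 59% |
| 5% | 90% |
| 10% | 99% |

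At 1%, no event would be seen 64% of the time. These limits apply to any zero count in 44 people, however the event is defined. They show that serious events will probably be sparse; they do not measure what is lost by counting reactions instead of events.

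**4. Non-serious events.** At assumed rates of 10% and 20%, the expected number of swimmers affected is 44 × 0.10 = 4.4 and 44 × 0.20 = 8.8. The ceiling on exposure is 44 × 8 = 352 participant-sessions, with full attendance. At such rates, non-serious events would give a trial of this size more usable safety information than serious ones. This supports the optional addition below; it does not show that the plan omits them.

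**The case against.** The strongest reply is that no serious event is lost. A reader might infer that events not attributed to swimming drop out of the trial. The Serious adverse event monitoring section rules that out: events are captured before attribution and go to the TSC with their classification. This stands, and it limits the point to the measure named for reporting.

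A reader might also infer that the trial cannot answer its own safety question. The documents do not support that either. Safety appears in the Background as a reason why research is needed. It is not in the aim or objectives, and the Criteria for success contain no safety threshold. Evaluation forms, interviews and coach focus groups may bring out harms. The service-use inventory also records health-care use in both arms at T0, T1 and T2, although it is not a safety record.

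Thirdly, the article condenses a fuller protocol and mentions a separate safety protocol; neither is shown. They may cover non-serious events and the way events are elicited in each arm, so the article's silence is not evidence of omission. This stands too, and is why non-serious events are only an optional part of the fix.

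What the reply does not remove is the choice of measure. The article states it, and it is narrower than the data described in its own monitoring section.

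**Conclusion.** The point holds as a mismatch between a named measure and the data behind it. As listed, the safety result rests on a causality judgement and offers essentially no between-arm comparison, so it serves the Background's safety rationale only weakly.

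This is a reporting weakness that is cheap to correct. It is not a failure of monitoring. It cannot be given a number, because the article states no event rates; the 8.0% limit for 0 of 44 is correct arithmetic but describes the sample size, not this defect.

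The conclusion rests on two assumptions: that reaction carries its usual meaning of an event attributed to the intervention, since the article does not define it, and that the full protocol does not already commit to reporting all serious events by arm.

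**What to change.** Under Secondary feasibility measures, replace the item with: *all serious adverse events in each arm, by count and type and whatever their cause, with those classified as possibly related to the study shown as a separate row.* This aligns the measure with Serious adverse event monitoring and uses events that the trial already identifies and classifies.

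Add one fixed survey item at T1 and T2, worded identically for both arms, asking about serious health events of any cause. An answer could reveal allocation to a research assistant helping by telephone, so place it last; Procedure already provides for another team member to take over if that happens.

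Optionally, and only if the full protocol does not already cover it, count non-serious swim-related events per participant-session, for example the signs of hypothermia that coaches already watch for. This needs a short new field on a coach form. The coach logs under Health economic measures record time and resources and would not serve as they stand.

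The cost is one survey item and, for the optional part, slightly more recording by coaches. N stays at 88 and no hypothesis test is added.
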